## Introduction

### Literature Review

More than 7000 lower limb amputations (LLAs) are performed in Canada each year due to (in order of decreasing prevalence) diabetic, vascular, traumatic, cancerous, and congenital indications [1]. Approximately 70% of these individuals will develop phantom limb pain (PLP) [2,3], a type of neuropathic pain where one experiences uncomfortable kinesthetic or somatosensory sensations in their missing limb following amputation [4]. PLP can be experienced for the first time within days following amputation (if not, within 1 year) and persists to variable degrees of intensity over a lifetime depending on the individual [5]. Research suggests that PLP is more likely to occur in people with more recent amputations compared to those who underwent amputations further in the past [2,3]. In addition, those who have an amputation due to chronic conditions (eg, vascular disease or diabetes mellitus) may have worse outcomes than those who undergo traumatic amputations because of preoperative factors (eg, preamputation pain) [2]. While PLP may improve over time if untreated, the lack of PLP treatment most often can significantly reduce quality of life, both psychologically and physically [6,7]. For example, research suggests PLP reduces mobility, which has adverse effects on independence (such as maintaining employment) and social role fulfillment [6,7]. PLP has also been implicated in a variety of other negative sequelae, including poorer sleep quality and increased depressive or anxious symptomatology [8-10]. The high prevalence of PLP among the growing number of LLAs, coupled with a lack of outpatient support, reflects an urgent need to develop effective treatments tailored to address the gap in care between the inpatient and outpatient settings to mitigate these negative sequelae.

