#### VR Intervention Procedure

Participants engaged in 1 VR session per day for approximately 20 minutes from their respective ward (orthopedic, vascular, or rehabilitation). At the beginning of the first VR session, after informed consent was obtained and the honorarium was given to the participant, the research assistant administered the sociodemographic and patient characteristic questionnaire (including age, amputation etiology, place of residence, etc). The research assistant then gave a brief verbal introduction to the VR-GMI system and instructed the participant on how to use the VR headset and handheld controls. Following VR instruction and at the beginning of each subsequent VR session, the research assistant verbally administered the Numerical Rating Scales (NRSs; 11-point Likert scales) for PLP, residual limb pain (RLP; ie, physical pain at the amputation site), and nausea before asking if they wanted to engage with the VR program that day. If they declined participation, their reason was recorded.

Participants were only permitted to engage in 1 stage per day. They could only move onto the next VR stage if their RLP, PLP, or nausea NRS scores did not increase by >2 points during or before their next session (given that treatment may exacerbate pain or nausea, and 3 points is considered a clinically significant increase) [44-47]. The participants were permitted to spend as much time as they preferred in each VR stage. If the participant chose to stop the session before the 20-minute goal (a session length used in previous studies) [23,48], the research assistant asked for and recorded their reason for discontinuation. Afterward, the research assistant verbally readministered the NRSs for PLP, RLP, and nausea. Any impromptu feedback or observations made by research personnel were recorded as field notes.

Participants were asked to engage in up to 10 VR-GMI sessions or until hospital discharge, whichever came first. After the last VR-GMI session, before discharge, the Igroup Presence Questionnaire (measuring VR immersion) [49] and VR Impressions Scale (developed by the laboratory for the purposes of descriptive evaluation of a VR intervention; Figure 3) [50] were administered.

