### Phase 4A: Hospital and Home Feasibility Study (Underway)

#### Overview

In phase 4A, the research team will assess the feasibility and pilot outcomes of the VR-GMI program in the acute postoperative period immediately following LLA (including the hospital and home). The research team aims to recruit 30 participants who recently underwent an LLA through the HSC. A research assistant will visit participants daily to administer the VR-GMI program for approximately 17 days. Participants will then be contacted again 1 month following their final VR session via phone call to assess postoperative PLP. Quantitative data will be collected to assess whether the VR-GMI program and study procedures are sufficient for an RCT.

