##### Pilot Outcomes

Participants who spend an extended amount of time in the VR-GMI program will report lower PLP incidence as well as (for individuals who have already experienced PLP onset) lower intensity and interference. These predictions are in line with previous research investigating prophylactic PLP treatment through mirror therapy in the postoperative period [23].

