#### Recruitment

The research team aims to recruit 30 participants, 5 (17%) of whom we expect to drop out and 25 (83%) to complete the program. This sample size is in line with previous pilot studies for PLP treatments that precede RCTs [38] and suits the descriptive and exploratory aims of the study. This sample size also has 80% power to detect the desired recruitment criterion [53].

Potential participants will be approached according to the recruitment strategies and eligibility criteria outlined and recommended in phase 3, with 3 exceptions to help mitigate recruitment barriers faced in the previous phase. First, clinical resource nurses on units where LLAs are treated at the HSC will be called each week to ascertain where eligible patients are to increase the recruitment rate. Second, individuals with bilateral amputations will also be eligible for recruitment, given preliminary data from phase 3 suggesting this may be feasible. Third, patients will be eligible to participate for up to 2 months following their LLA, in line with the literature that suggests such a time frame is suitable for the administration of acute PLP intervention [20].

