#### Data Analysis

Objectives 1, 2, and 4 will be evaluated descriptively via bar graphs, means, and SDs to compare each objective across administration settings and VR stage according to preset feasibility criteria. Preset feasibility criteria must be met to determine if the VR program is acceptable (mean Theoretical Framework of Acceptability Questionnaire score >3, which indicates a more favorable acceptability rating than no opinion; Sekhon et al [54]), tolerable (at least 70% of the participants do not report any pre- or post-NRS score increases of ≥3 for PLP, RLP, or nausea), and engaging (mean session duration ≥20 min). Similar progression criteria [52] must be met to determine whether procedural feasibility is appropriate for an RCT, including recruitment (at least 50% of the patients at the HSC who appear to meet the eligibility criteria will be screened through the established pathways), retention (at least 70% of the participants who live in Winnipeg will continue to participate in the study for as long as they are able to), and attrition (at least 80% of the participants will respond at the 1-month follow-up period following their final session) rate criteria. The sample will also be compared to the population of all people who underwent an LLA at the HSC during the recruitment period (from June 2024 to March 2025) via administrative chart review to evaluate whether the characteristics are relatively proportional to one another.

For objective 3, scatterplots will be generated to explore the association between the length of program engagement and the Brief Pain Inventory or Patient Reported Outcomes Measurement Information System pain interference. Mean or median difference in length of program engagement between participants who have and have not yet experienced PLP onset will also be calculated. If appropriate, exploratory regression models will be used to examine the effect of VR dosage on PLP outcomes.

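### The objective 3 onset contrast does not exclude phantom limb pain that began before the first VR session, and the dose analyses state no use of the first-session pain rating

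*Protocol article*

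**What the plan says.** Pilot Outcomes states the hypothesis: "Participants who spend an extended amount of time in the VR-GMI program will report lower PLP incidence". For people whose PLP has already begun, it predicts lower intensity and interference.

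Phase 4A, Data Analysis, sets out three analyses for objective 3:
- scatterplots of length of engagement against the Brief Pain Inventory or PROMIS interference score;
- a contrast of engagement by onset status: "Mean or median difference in length of program engagement between participants who have and have not yet experienced PLP onset will also be calculated";
- regression of PLP outcomes on VR dose, if appropriate, with no covariates named.

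Four other statements bear on these:
- Phase 4A, Recruitment: "patients will be eligible to participate for up to 2 months following their LLA".
- Introduction, Literature Review: "PLP can be experienced for the first time within days following amputation". The same section says that untreated PLP may improve over time.
- Phase 3, VR Intervention Procedure: PLP is rated on a numerical scale before the first and every later session, and the participant is then asked whether to use VR that day. Phase 4A, VR Intervention Procedures, keeps the phase 3 procedures apart from listed exceptions, and this rating is not among them.
- Phase 4A, Overview: "Participants will then be contacted again 1 month following their final VR session via phone call to assess postoperative PLP". VR use may last up to 17 days.

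**The concern.** The incidence hypothesis is about prevention, so it concerns only people who could still develop PLP when VR starts. The contrast as written also counts those whose PLP came first. In them, onset status is a baseline characteristic, and any link with engagement shows who tends to use VR rather than what VR does.

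The same applies to intensity and interference. Pain at the start predicts pain later, and a participant who has just rated their pain may decline the session or stop it early. Without the first-session rating in the analysis, a dose-pain slope mixes these influences with any effect.

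At stake is how the pilot dose-PLP relation is read when the later randomized trial is planned. The feasibility decision is not affected.

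**Working it through.** **Figures in the plan.** The sample size section says "The research team aims to recruit 30 participants, 5 (17%) of whom we expect to drop out and 25 (83%) to complete the program". Check: 25 / (1 − 5/30) = 30, which agrees. The only power statement is "This sample size also has 80% power to detect the desired recruitment criterion". It concerns recruitment, so objective 3 has no figure of its own to reproduce. All bias sizes below rest on assumed inputs.

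**Step 1: onset contrast with no VR effect.** Assumptions: 25 participants; engagement uniform over 1 to 17 days; PLP already present at the first session in 30%, 50% or 70%; onset hazard 0.01 per day in the rest; call 30 days after the last session. Participants with PLP at the start stop 5 or 3 days earlier, at the same time, or 3 days later than the others, always within days 1 to 17. Entries are mean engagement in the PLP group minus the no-PLP group, in days, with the share of samples below zero (the sign of a benefit) in brackets.

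| PLP at start | 5 days earlier | 3 days earlier | same | 3 days later |
|---|---|---|---|---|
| 30% | −1.99 (85%) | −1.14 (72%) | +0.41 (41%) | +1.95 (15%) |
| 50% | −2.85 (92%) | −1.73 (81%) | +0.33 (43%) | +2.38 (12%) |
| 70% | −3.42 (92%) | −2.09 (81%) | +0.26 (46%) | +2.67 (14%) |

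The sign follows the assumed link between baseline PLP and engagement. If they are unrelated, prior PLP creates no bias by itself. The small positive values in that column come from call timing (step 3).

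**Step 2: restriction to participants PLP-free at the first session.** With the call date as planned, the contrast is +0.65 to +0.70 days in every scenario. With a call at a common day 47 it is −0.03 to +0.03. Restriction therefore removes the part due to prior PLP and leaves a timing part.

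**Step 3: call timing.** Counting from the first session, a one-day user is called at about day 1 + 30 = 31 and a 17-day user at about day 17 + 30 = 47, a gap of 16 days.
- *Onset.* Longer users have more time to develop PLP. At hazard 0.01 per day the risk is 1 − exp(−0.31) = 27% by day 31 and 1 − exp(−0.47) = 37% by day 47. This points towards harm. Over hazards of 0.005 to 0.03 per day the contrast in PLP-free participants is +0.6 to +1.0 days.
- *Intensity.* If untreated PLP falls by g points per 30 days, the 17-day user scores g × 16/30 lower: 0.27, 0.53 and 1.07 points for g = 0.5, 1 and 2. This points towards benefit.

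**Step 4: baseline pain and the intensity slope.** Assumptions: baseline rating mean 5, SD 2; later score = 0.6 × baseline + 2 − g × (call day)/30 + noise of SD 1.5; g = 1; no VR effect. Entries are the 17-day minus 1-day difference in points.

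| Correlation of dose with baseline | Unadjusted, planned call | Adjusted, planned call | Unadjusted, day 47 | Adjusted, day 47 |
|---|---|---|---|---|
| 0 | −0.52 | −0.53 | 0.01 | 0.00 |
| −0.3 | −1.73 | −0.54 | −1.20 | 0.00 |
| −0.5 | −2.56 | −0.54 | −2.02 | 0.00 |

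Adjustment removes the baseline part and leaves the timing part. A positive correlation would reverse the sign of the baseline part.

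**The case against.** The strongest reply is that this is an exploratory objective in a condensed article, with descriptive plots and optional regression whose covariates are left open. Pilot Outcomes already separates people with prior onset for intensity and interference. Exploratory Outcomes plans to look at PLP by baseline variables, and the pre- and post-session ratings serve the tolerability criterion. This stands against any inference that the plan ignores baseline PLP. It does not answer the narrower point: the onset contrast is stated without a matching restriction, and baseline PLP is not examined jointly with dose.

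Three stronger readings are tempting, and the documents do not support them:
- *The analysis is set up to show benefit.* The documents give no direction for the link between baseline PLP and engagement. Discharge timing and residence outside Winnipeg also cut engagement short. Call timing works against benefit in the onset contrast.
- *Worsening pain cuts dose by rule.* The rule reads "They could only move onto the next VR stage if their RLP, PLP, or nausea NRS scores did not increase by >2 points". It limits the stage reached. Participants may stay in a stage as long as they like, so the rule alone does not shorten engagement. Declining a session or stopping early is the plausible route.
- *The false-positive rate can be stated.* That would need assumed correlations and a significance test that the plan does not include.

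A fixed call date would remove the timing part. However, the attrition criterion is defined by response 1 month after the final session, and 15 participants had been recruited by March 2025. A change now would alter that criterion and mix two schedules.

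**Conclusion.** The point holds in a limited form. The onset contrast includes PLP that VR could not have prevented, and the dose analyses state no use of a baseline rating that is collected. Whether this biases the result depends on an unknown, namely how engagement relates to baseline PLP. If the two are unrelated, only the timing part remains.

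Under the assumed inputs the onset contrast is about 1.1 to 3.4 days towards benefit if people with PLP at the start stop 3 to 5 days earlier, and about 2.0 to 2.7 days towards harm if they stay 3 days longer. Call timing adds an apparent gain of 0.27 to 1.07 points in intensity if PLP improves untreated by 0.5 to 2 points per 30 days. None of these sizes can be derived from the documents.

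Severity is minor. Objective 3 is exploratory, none of the preset feasibility criteria uses it, and efficacy is left to a later randomized trial.

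**What to change.** Change the objective 3 paragraph of Phase 4A, Data Analysis, as follows:

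1. Report the onset contrast among participants with no PLP reported up to the first session, with counts, and show those with prior PLP separately. A zero rating on the day does not rule out earlier PLP that resolved, so state how prior PLP is established.
2. Adjust or stratify the intensity and interference plots, and any regression, by the first-session PLP rating.
3. Report days from amputation and from first session to the call. State that this timing is largely confounded with calendar length of engagement, so adjustment cannot readily separate the two.
4. Describe the results as association rather than as an effect of dose.

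The follow-up schedule stays as it is, so the timing part in steps 2 to 4 of the working remains and has to be acknowledged.

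The rating is already collected. The main cost is a small PLP-free subset: with 25 completers and an assumed 30% to 70% with PLP at the start, 25 × 0.7 = 17.5 down to 25 × 0.3 = 7.5 participants. In the simulation with the planned call date, the SD of the onset contrast rises from about 1.9 to 2.5 days to about 2.5 to 4.1 days. If the protocol does not already record PLP history at entry, one question has to be added.

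### The phase 4A incidence hypothesis is firmly analysed only as engagement time by PLP onset status, which gives no incidence by dose and leaves mean or median open

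*Protocol article*

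**What the plan says.** The Pilot Outcomes section of phase 4A (objective 3) makes program time the exposure and PLP the outcome: "Participants who spend an extended amount of time in the VR-GMI program will report lower PLP incidence". For people whose PLP has already started, it predicts lower intensity and interference.

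The phase 4A Data Analysis section gives three elements for this objective:

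- For pain scores: "scatterplots will be generated to explore the association between the length of program engagement and the Brief Pain Inventory", or against the PROMIS interference score. Onset is not plotted.
- For onset: "Mean or median difference in length of program engagement between participants who have and have not yet experienced PLP onset will also be calculated".
- For dose to outcome: "If appropriate, exploratory regression models will be used to examine the effect of VR dosage on PLP outcomes". The condition, the model and the outcomes are not named.

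The same section opens with "Objectives 1, 2, and 4 will be evaluated descriptively via bar graphs, means, and SDs", so the general descriptive summaries are assigned to the other three objectives.

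**The concern.** The hypothesis runs from dose to incidence. The firm onset analysis runs the other way: it splits participants by outcome and compares their exposure. Its result is a number of minutes. A reader who wants to know what proportion developed PLP at low and at high engagement will not find that in the committed output, although the data for it are collected.

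Two features add to this.

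- **Choice of summary.** Mean and median are offered as alternatives. Exposure is likely to be uneven: people living outside Winnipeg stop at discharge, others may continue for up to 17 days, and the phase 3 procedures carried forward let participants stay in a stage as long as they like. Under such a distribution the two summaries can disagree.
- **Onset before treatment.** Phase 4A admits patients up to 2 months after amputation, and the Literature Review says PLP can begin within days. The group with onset can therefore include people whose PLP began before any VR session. Their later engagement cannot bear on whether PLP started.

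At stake is how informative the pilot outcome is. The feasibility conclusions are not affected.

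**Working it through.** **Inputs from the article.** Sample: "The research team aims to recruit 30 participants, 5 (17%) of whom we expect to drop out and 25 (83%) to complete the program"; 25/30 = 83%, which is consistent. Background rate: "Approximately 70% of these individuals will develop phantom limb pain (PLP"; 17/25 = 68% is used as the nearest round case. Typical full dose: 17 days × about 20 min = 340 min. The article gives no engagement distribution, so all minutes below are illustrative. Gaps are mean or median without onset minus with onset; a positive gap agrees with the hypothesis.

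**1. The gap is not a measure of risk.** Take 12 participants at a low dose of 100 min and 13 at a high dose of 300 min, with onset in 10/12 (83%) and 7/13 (54%).

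- Mean without onset: (2×100 + 6×300)/8 = 250 min.
- Mean with onset: (10×100 + 7×300)/17 = 182.4 min.
- Gap: 67.6 min.

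With two dose values the gap equals (high − low) × (6/8 − 7/17) = 200 × 0.338. Move the high dose to 340 min and leave every onset count unchanged: 240 × 0.338 = 81.2 min. The incidences are identical, but the gap differs because it also depends on the spread of dose.

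**2. The gap does not give incidence by dose.** Space engagement evenly over 60-300 min in those with onset and over 100-340 min in those without. Mean and median are then 180 and 220 min, a gap of +40 on both summaries.

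| Onset cases | Below 200 min | 200 min or more |
|---|---|---|
| 17 of 25 | 10/13 = 77% | 7/12 = 58% |
| 8 of 25 | 5/12 = 42% | 3/13 = 23% |

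The gap is the same and the incidence levels are quite different. The difference between levels is about 19 points in both rows, and the group sizes would show that the overall rates differ.

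**3. Mean and median can conflict.** With onset (n = 17): 60×3, 100×5, 160×5, 340×4 (minutes × people). The sum is 2840, mean 167.1, median 160. Without onset (n = 8): 40×3, 180×3, 200×2. The sum is 1060, mean 132.5, median 180. The mean gap is 132.5 − 167.1 = -34.6 min and the median gap is 180 − 160 = +20 min. No one exceeds 340 min.

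**4. How often.** Simulation used 20,000 trials per setting, n = 25 or 30, and PLP 50% or 70%. Assumptions not in the article: 60% Winnipeg residents with 8-17 sessions, others with 1-8, and about 20 (SD 6) min per session.

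| Log-odds of PLP per SD of dose | Mean and median of opposite sign |
|---|---|
| 0 | about 18% |
| -0.5 | 9-10% |
| -1 | 1-2% |

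In up to 500 trials per setting a logistic regression of PLP on dose was also fitted. Its slope agreed in direction with the mean difference every time.

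**5. Precision of the replacement.** Wilson 95% interval for 10/12: centre (0.833 + 3.84/24)/(1 + 3.84/12) = 0.753; half-width 1.96 × √(0.833×0.167/12 + 3.84/(4×144))/1.320 = 0.200; so 55% to 95%. The same formula gives 29% to 77% for 7/13. The Newcombe 95% interval for the 29-point difference is -7 to +57 points.

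**The case against.** The case against is substantial, and much of it stands.

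- **A reader might infer that incidence by dose is never estimated.** The article does not support that. The sentence after the onset comparison plans regression of PLP outcomes on dosage, and incidence is the first such outcome in the hypothesis. What remains is that this is conditional and does not name incidence.
- **A reader might call the comparison backwards, or say the hypothesis cannot be answered.** That is too strong. Comparing a continuous exposure between outcome groups is a valid measure of association, and its mean version gave the direction of the logistic slope in every simulated trial fitted. It informs on direction, not on incidence.
- **A reader might infer that no overall incidence will be available.** The two group sizes give it. The Exploratory Outcomes section also looks at PLP incidence across baseline and sociodemographic variables, under an objective that is to be summarised descriptively.
- **A reader might argue that one mean gap fits both a large effect and none.** An example exists: onset in 8/12 at 100 min and 9/13 at 300 min, with one onset-free user moved to 900 min, has a mean gap of 275 − 205.9 = 69.1 min. It depends wholly on that user, who would need 900/17 = 53 min every day. At 340 min the gap is (4×100 + 3×300 + 340)/8 − 205.9 = 205 − 205.9 = -0.9 min. It should not be relied on.
- **A reader might say the planned RCT needs this event rate.** Nothing in the article says so. The RCT protocol is separate.
- **Scope.** The aims are described as descriptive and exploratory, no progression criterion rests on objective 3, and a rule for mean versus median could sit in an analysis plan. This lowers the weight of the open choice. It does not remove the mismatch between the stated hypothesis and the stated firm analysis.
- **Dose bands discard information at this size.** True, so the regression should keep dose continuous and the bands should serve for description only.

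**Conclusion.** The point holds in a limited form. The hypothesis concerns incidence by time in the program. The only firmly planned onset analysis is a comparison of engagement by onset status, which is valid as description but supplies no incidence by dose. The one dose-to-outcome analysis is conditional and does not name onset.

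The open choice of summary matters at about 25 participants. The sign can differ without any extreme user, but sign conflict is common (about 18%) only where there is no association and the direction is noise anyway. It falls to 1-2% with a strong association. Those rates rest on an assumed engagement distribution.

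The status split also mixes onset before and after the first session, so it is not incidence during or after treatment. The weight is modest: this improves an exploratory outcome and leaves the feasibility criteria untouched.

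**What to change.** Reword the objective 3 analysis as follows.

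1. As the main incidence summary, report the number and percentage with PLP onset, overall and by engagement level, with levels set in advance and exact or Wilson 95% intervals.
2. Restrict that summary to participants without PLP onset before their first session, and report the number excluded for this reason.
3. Name PLP onset as an outcome of the exploratory regression, with dose kept continuous.
4. Keep the engagement comparison as a secondary description with one summary fixed in advance, for example the median with interquartile range given the uneven exposure.
5. Label all of this exploratory, and state that dose is confounded by time of discharge and place of residence.

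The cost is analysis wording; the only data need is onset status before the first session. The downside is precision. Intervals of the width shown above are to be expected with 25 people, and wider ones after the restriction in item 2. The article does not say how many will already have PLP at entry. If it were a quarter to a half (an assumption), 25 × 0.75 ≈ 19 down to 25 × 0.5 ≈ 12 would remain.
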